## Abstract

**Background:**

Pharmacological intervention is essential for managing the symptoms of Parkinson's disease. Adherence to medication regimens however is a major problem. Poor adherence leads to significant motor deterioration and inadequate symptom control. This results in poor quality of life. Whilst interventions to improve medication adherence have shown considerable benefit in other chronic conditions, the efficacy of such treatments in Parkinson's disease is less well researched. Many people with Parkinson's disease require substantial support from spouse/caregivers. This often extends to medication taking. Consequently, spouse/caregiver's support for timely medication management is paramount. We aim to investigate the benefit of a novel intervention, Carer Assisted Adherence Therapy, for improving medication adherence and quality of life in people with Parkinson's disease. Adherence therapy may help to optimise the efficacy of anti-parkinsonian agents, subsequently improving clinical outcomes.

**Methods/Design:**

A parallel, randomised controlled trial will be conducted to investigate whether carer assisted adherence therapy is effective for improving medication adherence and quality of life. We aim to recruit 40 patient/carer pairs into each group. Participants will be randomly assigned by the Clinical Research Trials Unit at the University of East Anglia. Adherence therapy is a brief cognitive-behavioural approach aimed at facilitating a process of shared decision making. The central theory is that when patients make shared choices with a professional they are more likely to continue with those choices because they are personally owned and meaningful. Outcomes will be rates of adherence and quality of life, determined by the Morisky Medication Adherence Scale-4 and the Parkinson's disease Questionnaire-39 respectively. Assessments will take place post randomisation, immediately post intervention and 12-weeks post randomisation. Primary outcomes are adherence and quality of life at 12-week follow-up. Efficacy will be determined using intention-to-treat analysis. Independent samples t-tests will compare mean changes between groups from baseline to follow-up. Per protocol analysis will be conducted based on individuals with no major protocol deviation. Where imbalances in baseline characteristics are identified, an adjusted analysis will be performed using a regression model. Analysis will be masked to treatment allocation.

**Trial Registration:**

ISRCTN: ISRCTN07830951

## Background

### Parkinson's disease

Parkinson's disease (PD) is a progressive, disabling, neurodegenerative disease that significantly reduces quality of life (QoL) [1,2]. Debilitating symptoms of bradykinesia (slowness of movement), resting tremor, rigidity and postural instability are principal features of PD [1,3]. In addition to these motor symptoms, non-motor symptoms (NMS) such as cognitive impairment, dementia, sleep disturbances, depression and falls are significantly associated with reduced QoL [4]. Cognitive impairment is reported to affect 20-30% of patients with PD, even in the early stages of the disease [5]. As PD progresses cognitive decline persists and patients may develop dementia [6]. The cumulative prevalence has been reported to be substantial; at least 75% of people with PD who survive longer than 10 years will develop dementia [6]. As motor and NMS have considerable impact on QoL in PD, addressing both is therefore an integral part of management.

### Treatment & Regimen Complexity

The pharmacological management of PD is complex. Monoamine Oxidase-B (MAO-B) inhibitors, dopamine receptor agonists and Levodopa represent first line treatment options [1]. Typically younger individuals are treated with a MAO-B inhibitor (one daily dose), especially if symptoms are mild, or a dopamine receptor agonist (three daily doses) as first line intervention. Older (≥ 75 years) individuals, especially those with or at risk of cognitive impairment, may be treated with Levodopa as first line therapy [7,8]. Although management in early disease is usually adequate with monotherapy [7,8], more than half of people with PD take two to four anti-parkinsonian medications three to four times daily [9,10]. This is because multiple drug classes are warranted as PD progresses [11-14]. Furthermore, each drug may have different dosing schedules, further complicating regimens [9]. Catechol-O-Methyltransferase inhibitors can supplement Levodopa adding further complexity. Increasing doses and/or dosage frequency may also be required to adequately manage worsening symptoms in advanced stages [14]. With advancing disease, the therapeutic window narrows and becomes reliant on more frequent and specific interval dosing to maintain adequate treatment effect and avoid motor fluctuations [7,15]. Some people with advanced PD can take as many as ten doses a day in order to manage fluctuations [8,16]. Dyskinesias (involuntary movements) associated with long-term Levodopa use may also require remediation in later PD [16]. Additionally, specific non-motor complications necessitate further drug use [4,14].

### Medication Non-adherence

To achieve optimal symptom control, adherence to medication in PD is paramount [17]. However, it has been reported that a third to half of all medicines prescribed to people with long-term conditions are not taken as recommended [18-20]. Therefore, not surprisingly medication adherence is poor in people with PD, especially as symptoms of cognitive impairment and anxiety and depression have been reported to be highly prevalent and which impact negatively on medication adherence in this patient population [21]. Reported medication adherence in PD was as low as 10% in one study with 76% acknowledging miss-timed or missed doses [22]. For drugs requiring multiple daily doses, researchers reported only 3% fully adhered to medication regimens [23]. These findings suggest medication non-adherence is significant in people with PD. The consequences of non-adherence are substantial [24]. Poor adherence can result in wearing off of the treatment effect which can significantly increase motor dysfunction [15]. People with PD may also over-medicate with dopaminergic therapy [23]. This can result in severe dyskinesia, potentially lead to the development of impulse control disorder, especially when dopamine receptor agonists are used, and may even result in psychosis [25]. Dyskinesias have been associated with significant reductions in QoL [26].

### Carer Involvement

Although people may be completely independent in the early stages of PD, in advanced stages people usually require considerable support with daily activities [27]. Many people with PD receive support through informal carers such as a spouse or family member. This often extends to medication management, particularly aiding in the taking of medications [16,28]. For the caregiver, the responsibility for and help with timely management of a relative's anti-parkinsonian medication is essential [27].

### Study Rationale

There is a need for an intervention that enhances adherence to prescribed medication in PD. A targeted therapy is likely to be associated with overall improvement in rates of adherence, leading to optimal symptom control. Increasing motor fluctuations and dyskinesias resulting in disability have been associated with poor QoL [26]. As common motor symptoms of bradykinesia and rigidity are sensitive to anti-parkinsonian therapies [8], improved adherence to anti-parkinsonian medication may facilitate a mechanism for improving QoL.

Interventions aiming to improve adherence have demonstrated efficacy in other long-term conditions such as hypertension and psychotic disorders [29-32]. However, there is a paucity of evidence testing the efficacy of adherence interventions in PD. Previous research has identified a variety of factors that influence non-adherence in PD: problems with complex treatment regimens, polypharmacy, cognitive impairment and depressive symptoms [15,16,33,34]. Therefore, a patient centred therapy aimed at exploring personally relevant benefits of medication use, formulating problem solving strategies and exploring beliefs and concerns about medications may improve adherence to anti-parkinsonian drugs. It is also acknowledged that in PD caregiver involvement in fostering medication adherence can be substantial [16]. This is essential where significant cognitive impairment presents. Therefore, caregivers need to be supported in their role of encouraging medication adherence.

We hypothesise that an adherence therapy that targets both people with PD and their spouse/carer is likely to improve medication adherence and be associated with better QoL compared to treatment as usual.

## Methods/Design

### Trial Design

A parallel group, randomised controlled trial will be conducted to compare Carer Assisted Adherence Therapy (CAAT-PARK) with Treatment as Usual (TAU) for non-adherent people with PD and their spouse/carers. The study will compare the two groups immediately post intervention and at 12 weeks post randomisation (follow-up).

### Trial Objectives

To investigate whether people with PD and their spouses/carer who receive a programme of CAAT-PARK in addition to TAU show significantly greater rates of medication adherence and improved QoL from baseline to 12 week post randomisation compared to those who receive TAU only.

Secondary objectives are to investigate whether people who receive CAAT-PARK and those who receive TAU differ in terms of overall disease state, activities of daily living (ADL), beliefs about medication, generic health related QoL, and levels of carer distress. We will investigate whether baseline levels of cognitive impairment and anxiety and depression influence the effective uptake of CAAT-PARK. We also aim to investigate the experience of those receiving the intervention.

### Outcome Measures

#### Primary outcomes

• Change in adherence to medication determined by the Morisky Medication Adherence Scale (MMAS-4) [35]

• Change in QoL determined by the Parkinson's Disease Questionnaire-39 (PDQ-39) [36]

#### Secondary outcomes

People with PD:

• Movement Disorder Society - Unified Parkinson's Disease Rating Scale (MDS-UPDRS) Part I (non-motor experiences of daily living), Part II (motor experiences of daily living) and Part IV (motor complications) [37]

• Beliefs about Medication Questionnaire (BMQ) [38]

• EuroQol quality of life questionnaire (EQ-5D) [39]

Spouse/Carer Outcomes:

• Carer Distress Scale (CDS) [40]

• BMQ

### Trial Participants

People attending Medicine for the Elderly or Neurology outpatient appointments at a University Hospital in the East of England, UK, for diagnosed or probable PD. Spouse/carers will be invited to participate.

### Inclusion Criteria

1. Adults diagnosed with, or with probable, Idiopathic PD (three out of four of the chief UK Brain Bank criteria).

2. Prescribed one or more anti-parkinsonian medications by a Consultant Neurologist or Consultant Physician with specialist knowledge of movement disorders.

3. English speaking and literate (participants are required to actively engage in the therapy process).

4. Stable medication regime i.e. not altered within the previous month and not expected to change during the period of the research project (12 weeks).

5. Not demented or significantly cognitively impaired. The clinical team will judge whether the patient has the cognitive capacity required to participate fully in the trial i.e. read patient information, complete self report questionnaires and engage actively in the therapy process.

6. Show poor adherence as determined by a MMAS-4 score ≥ 2.

### Exclusion Criteria

1. Suspected Parkinsonism due to other causes than idiopathic PD.

2. Treated with anti-parkinsonian medications for a mental health complaint.

3. Diagnosed with dementia.

4. Life expectancy < 6 months.

### Recruitment

People who are potentially eligible based on inclusion criteria 1, 2, 3, 4 and 5 will be identified by the clinical team two weeks prior to upcoming outpatient appointments. An information pack containing: a patient invitation letter, participant information sheet, MMAS-4 and a consent form for the MMAS-4 will be posted out to those who are potentially eligible. This represents stage one consent i.e. willingness to consider study participation. An information sheet for the spouse/carer will supplement the patient information. Patients will be asked to return the MMAS-4 and the accompanying consent form. People scoring ≥ 2 will be informed by phone of their suitability to participate. Individuals who are willing to participate but do not meet eligibility criteria will be thanked for their interest. Eligible patients will be approached for their consent to participate in the trial on the day they attend clinic for their out-patient appointment (stage two consent). Recruitment will be a rolling programme over 12 - 14 months until recruitment targets are achieved. Figure 1 shows the CONSORT diagram for progression of participants throughout the study duration.

**Figure 1 F1:**
[figure not shown]
**CONSORT diagram - progression through CAAT-PARK**.

### Informed Consent

Thirty minutes will be set aside for taking informed consent to ensure patients/carers possess a sound understanding of the trial. At each point of participant contact ongoing verbal consent will be sought. If patients withdraw they will then receive standard care (TAU). Data collected to the point of withdrawal will be retained in the trial data set.

### Randomisation

Participants will be randomly assigned to CAAT-PARK or TAU. Randomisation will take place in a private room following signed informed consent and completion of baseline (pre-randomisation) measures. Randomisation will be completed using computer generated random numbers accessed via a web-based randomisation system developed by the Clinical Research Trials Unit (CRTU) at the University of East Anglia (UEA). Participants will be allocated a unique identifier number which will be sent to CRTU where allocation will be undertaken by permuted random blocks of four and six. Participants will be stratified into spouse/carer present or no spouse/carer present groups at randomisation respectively in order to investigate the potential effect modification of the spouse/carer on the treatment effect. The trial medical statistician ([name]) assisting in the analysis of all study data will be masked to participant group allocation.

### Baseline Assessments

Once the patient has consented some of the baseline data will be collected prior to randomisation. Baseline measures for primary outcomes (MMAS-4, PDQ-39) will be completed by participants at this stage to ensure data is acquired prior to randomisation. Participants will also be assessed in clinic prior to randomisation using measures that cannot be self-reported and require a rater, MDS-UPDRS parts I & IV and the Montreal Cognitive Assessment (MoCA). The Hospital Anxiety & Depression Scale (HADS) will also be completed at this stage. All scales will be completed in a private consultation room. Participants will be instructed how to complete all other baseline measures for secondary outcomes before taking them home to complete in their own time: BMQ, EQ-5D and MDS-UPDRS part II (patient questionnaire). Spouse/carers will take the baseline BMQ and CDS home to complete. Participants will be asked to return these self-reported questionnaires within two weeks of randomisation. The following information will be obtained:

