**Figure 3 F3:**
[figure not shown]
**CAAT-PARK model**.

Participants allocated to CAAT-PARK will receive seven 30 minute sessions at weekly intervals. Assessment and problem solving will be delivered twice, making up seven sessions in total. Each weekly session will incorporate a separate theme, however, each session will be participant centred. Where a patient's carer has consented to the trial, the intervention will be delivered to the carer at the same time. Ten sessions over the course of the trial will be recorded to determine treatment fidelity against the CAAT-PARK manual [49].

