### Study Limitations

The subjective nature of the self report instruments used for evaluation of CAAT-PARK is acknowledged and every effort will be made to minimise this potential bias. In particular, patients may over or under report their true health status depending on the trial arm to which they are assigned. Baseline primary outcome measures will be completed prior to randomisation in attempt to reduce this bias. Resulting from the one-to-one participatory nature of CAAT-PARK, it will not be possible to mask study participants to their group allocation. Therefore, secondary outcomes at baseline (completed post randomisation) and all follow-up study outcomes will not be blinded.

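### Baselines for several secondary outcomes, including both listed carer outcomes, are completed after allocation is known, so any analysis that uses them as baselines is open to bias

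*Protocol article*

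**What the plan says.** Baseline Assessments splits the baseline in two. MMAS-4, PDQ-39, MDS-UPDRS parts I and IV, MoCA and HADS are done in clinic before randomisation. Patients take the BMQ, EQ-5D and MDS-UPDRS part II home. For carers: "Spouse/carers will take the baseline BMQ and CDS home to complete". The timing is then given as: "Participants will be asked to return these self-reported questionnaires within two weeks of randomisation".

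Randomisation takes place in a private room, "following signed informed consent and completion of baseline (pre-randomisation) measures". Study Limitations says that "it will not be possible to mask study participants to their group allocation", and concludes that "secondary outcomes at baseline (completed post randomisation) and all follow-up study outcomes will not be blinded". The same section accepts that patients' reports may depend on the arm they are in, and gives pre-randomisation completion of the primary baselines as the safeguard.

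On therapy, the Intervention section says: "Participants allocated to CAAT-PARK will receive seven 30 minute sessions at weekly intervals". Carers who have consented receive it alongside the patient. Modifying beliefs about medication is named as a central element. Follow-up Measurements puts the post-intervention assessment at week seven or eight in the CAAT-PARK arm, and presents the repeated baseline measures as the means of judging efficacy.

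**The concern.** A baseline is safe to subtract or adjust for because allocation cannot have influenced it. These five forms (three patient, two carer) do not meet that condition. A participant who has just learned the allocation may answer differently. A CAAT-PARK participant may also have begun a therapy aimed at what the BMQ measures.

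The outcomes involved serve stated secondary objectives: activities of daily living, beliefs about medication, generic quality of life and carer distress. BMQ and CDS are the only carer outcomes listed, so no carer outcome in this carer-assisted trial has a pre-randomisation baseline.

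The protocol also compares baseline characteristics between arms and adjusts for imbalances. If these forms entered that step, a reaction to allocation could be mistaken for chance imbalance and adjusted for.

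**Working it through.** No stated figure in the protocol bears on this point, so there is nothing to reproduce. The check is one of timing, followed by arithmetic on assumed shifts.

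**1. Order of events**

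| Step | Measures | Allocation known? |
|---|---|---|
| Clinic, before randomisation | MMAS-4, PDQ-39, MDS-UPDRS I and IV, MoCA, HADS | No |
| Randomisation, same visit | – | – |
| Home, returned within two weeks | Patient BMQ, EQ-5D, MDS-UPDRS II; carer BMQ, CDS | Yes |

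**2. Overlap with therapy.** Seven weekly sessions with an assessment at week seven or eight imply a start at about week 1, although no first-session date is given. At most about two sessions could precede the return deadline: 2/7 = 28.6%. If the effect accrued linearly and each form were completed at the deadline, a change score would recover 1 − 2/7 = 71% of it. Both conditions are assumptions.

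**3. Algebra.** Scale each outcome to SD 1, with baseline-to-week-12 correlation ρ. Let τ be the true week-12 effect, r the arm difference in week-12 reporting due to unblinded response, and s the arm difference in the baseline form caused by allocation or early therapy. The expected contrast, CAAT-PARK minus TAU, is:

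- change score: τ + r − s
- ANCOVA on this baseline: about τ + r − ρs
- week-12 scores alone: τ + r

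If the reaction affects the baseline only (r = 0), the change score is off by the whole of s and ANCOVA by about ρs.

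**4. Illustration.** The simulation used 4,000 runs per setting, 40 per arm (from Sample Size), τ = 0 and r = 0. The values of s and ρ are assumed. Each cell gives the bias in SD and the rejection rate at nominal 5%.

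| s | ρ | Change score | ANCOVA | Week 12 only |
|---|---|---|---|---|
| 0.1 | 0.5 | −0.103; 7.7% | −0.054; 5.9% | −0.005; 4.7% |
| 0.1 | 0.7 | −0.103; 9.0% | −0.073; 7.1% | −0.002; 4.5% |
| 0.2 | 0.5 | −0.201; 14.1% | −0.099; 8.0% | 0.003; 5.1% |
| 0.2 | 0.7 | −0.202; 21.3% | −0.142; 13.9% | −0.001; 5.3% |
| 0.3 | 0.5 | −0.293; 25.8% | −0.146; 11.7% | 0.001; 5.3% |
| 0.3 | 0.7 | −0.300; 39.6% | −0.211; 23.7% | −0.003; 5.2% |

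Hand check for s = 0.2, ρ = 0.5: the SD of change is √(2(1 − 0.5)) = 1, so the standard error is √(2/40) = 0.224 and 0.2/0.224 = 0.894. By the normal approximation the rejection rate is 1 − Φ(1.96 − 0.894) + Φ(−1.96 − 0.894) ≈ 14.5%, in line with the simulated 14.1%.

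**5. Direction.** Early benefit in the CAAT-PARK forms would shrink the apparent change. Worse reporting at baseline in that arm would inflate it. The documents do not settle which would dominate.

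**The case against.** The strongest reply is that the protocol does not prescribe a change analysis for these outcomes. The mean-change t-test is described under Efficacy Analysis of Primary Outcomes, and in the abstract it follows the primary-outcome sentence. Only the intention-to-treat principle is extended to all outcomes, and the secondary objectives ask simply whether the groups differ. This stands: the point applies to any analysis that uses these baselines, and it cannot be said that a biased analysis has been specified.

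The magnitude can also be challenged. Two weeks is a return deadline, so many forms may be completed sooner. The five therapy phases are listed with assessment first and beliefs last, so if delivery follows that order, little belief work falls in the first two sessions and linear accrual is doubtful for the BMQ. A reporting reaction that persists to week 12 would partly cancel in a change score, because follow-up is unblinded too. All of this stands, and it makes the figures above illustrations only.

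A reader might also infer that the Randomisation section contradicts Baseline Assessments by placing all baseline measures before allocation. It does not: its parenthesis limits the statement to the pre-randomisation measures, and Baseline Assessments says that only some of the data are collected by then.

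Finally, the limitation is disclosed and the primary outcomes are protected. That lowers the severity. It does not remove the problem, because the protocol's own reason for protecting the primary baselines applies equally to the forms sent home.

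**Conclusion.** The point holds for the patient BMQ, EQ-5D and MDS-UPDRS part II and for the carer BMQ and CDS. Their baselines are post-allocation and unblinded on the protocol's own statement. Using them as a baseline, as a covariate or as evidence of imbalance opens the result to bias of unknown size and direction.

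The relation of s SD of shift to s SD of bias in change is exact only if the shift is confined to the baseline. The 29% and the 0.1 to 0.3 SD shifts are assumptions, since the documents give neither a first-session date nor a shift size.

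A reader might go further and conclude that randomisation no longer protects the comparison on these outcomes. The documents do not support that: week-12 scores compared by arm remain a randomised comparison, subject to the unblinded reporting already acknowledged. The primary analyses and the sample size are not touched. This should be fixed, but the trial's main conclusion does not depend on it.

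**What to change.** **Participants still to be enrolled.** Have the five self-report forms completed after stage-two consent and before the web randomisation is triggered, preferably at the clinic visit. The cost is a longer visit, on top of thirty minutes for consent and the existing assessments. Taking the forms home and randomising on their return would also work, but it gives up same-visit randomisation and may lose some consented participants. Trial Status puts recruitment at 16% of target at submission, so on that figure most participants could still be covered.

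**Participants already randomised.** Compare week-12 scores by arm, adjusting only for variables measured before randomisation, such as PDQ-39, HADS, MoCA and the carer stratum. Do not use the post-allocation forms as a baseline or covariate, or in the imbalance check. Record each form's completion date relative to randomisation and the first session. Using the same week-12 model for everyone avoids mixing two kinds of baseline; forms collected under the new order can support a sensitivity analysis.

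The analysis change needs no new data, but it costs some precision. Against ANCOVA with a clean baseline, an unadjusted week-12 comparison has a standard error larger by a factor of 1/√(1 − ρ²), which is 1.15 at ρ = 0.5 and 1.40 at ρ = 0.7 (assumed correlations). The pre-randomisation covariates should recover part of this. The change does not remove unblinded reporting at week 12, which remains a stated limitation.
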